***D.2.4. Data Quality Control***

*In this section we describe several procedures to ensure data quality and estimate the extent of measurement error for the various outcome measurements and confounding factors. Key to ensuring high quality data will be extensive training of the team of interviewers, and supervision during data collection and data entry. The 3 area supervisors (see Figure 4) will verify all forms for accuracy and completeness on a routine basis before data entry at INSP, and incorrect or incomplete entries will be corrected as far as possible during data collection. Further, to avoid systematic biases, all interviewers within each area of measurement will be randomly assigned to subjects using computer based algorithms as in our previous studies. Estimates of validity and reliability will be obtained for selected measurements by collecting either duplicate measurements by supervisors blinded to the interviewers’ observations and/or additional data on study subjects or comparable non-participants as described below.*

1. *A supervisor will verify measurements in a 10% random subsample for a) maternal and child* ***anthropometry****; b) birth outcomes; c) sociodemographic characteristics and obstetric history status; and d) infant feeding practices. These measurements will be done within 1-2 days of the original measurement. Data collectors will not know in advance which subsample is being verified.*

*2) The accuracy of estimates of* ***gestational age*** *obtained at birth will be validated by comparing them to estimates obtained from ultrasound examinations to be conducted during the routine prenatal visit at approximately 32 weeks gestation in a 10% random subsample.*

*3) For* ***psychological assessments*** *(infant neurodevelopment, maternal intelligence and home environment) and dietary intakes (24 hour recalls for mothers and infants), the supervisors will verify data quality as follows:*

1. *A 10% random sub-sample of subjects will be interviewed independently at the different time points by the supervisor. Data collectors will not be aware of the sub-sample being verified.*
2. *A different 10% subsample of interviews will be directly supervised during the interviews.*

*4) In the case of* ***biochemical estimations***

1. *Duplicate aliquots for a 10% subsample of blood and breast milk samples will be analyzed at Nutrek, Inc Essential Fatty Acid laboratory, Brookline, MA, USA (see Appendix V.)*
2. *All samples will be carefully labeled (type of specimen, identification number and date of collection) using indelible markers and frozen on the same day of collection at INSP after separation and preparation of aliquots. Dry ice will be used for transportation and the temperatures of storage freezers will be checked daily.*
3. *All lab personnel will be blinded to the supplementation codes and all estimations will be done by the same chemist highly trained and experienced in gas chromatography. High quality external standards will be procured and the maximum allowable CV will be 18% for each fatty acid.*

*Measurement error will also be estimated for the key outcome measures of infant development in an independent sample of age-appropriate mother-child pairs (n=30) living in the same general area of the study population, who are not participating in the main study. All the examiners and area supervisors will obtain replicate, blinded measurements within the same week, with the order in which they conduct the interviewers to be assigned at random. Standard methods will be used to calculate the inter-rater reliability coefficient[[225]](#endnote-225) to estimate the degree of error. Using methods originally developed in nutritional epidemiology to account for within-subject variability and measurement error in dietary intakes[[226]](#endnote-226) we will correct effect estimates for the observed measurement error[[227]](#endnote-227).*

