In terms of the main outcomes of interest, namely infant growth and development, mean (S.D) weight and length at birth were 3.18 (0.46) kg and 49.59 (2.29) cm, respectively (n=126). As expected, linear growth retardation continued in the first year of lifeError: Reference source not found (mean length for age Z score at 12 months was –0.68). Motor and mental development, measured using the Bayley Scales of development during the first year of life in the same cohort of infants, are presented in Table 2. Interscorer agreement/inter-tester reliability was above 90%. Although sample size limits our ability to make definitive conclusions, Bayley scores at 12 months of age were higher among infants whose mothers had higher intakes of DHA. Differences of 4-5 points were seen for both the mental development (MDI) and psychomotor (PDI) indices among infants whose mothers consumed at least 0.1 g of DHA in the third trimester of pregnancy, compared to those who consumed less. Linear regression analyses also show that MDI at 12 months of age increased by 18.8 points per % total fatty acids change in maternal DHA intake during pregnancy (p=0.07, n=78), adjusting for total energy and the ratio of AA (n-6) to DHA (n-3) dietary intake. Cord blood DHA was also a significant predictor of MDI at 12 months of age (regression coefficient=15.24 points/ % of total fatty acids in cord blood; p=0.03, n=21).

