weekly basis to distribute supplements and monitor compliance. *These workers will have a minimum qualification of having completed high school and will be trained to provide referrals for health care if required.* We expect about 100 - 400 women in the study per month and each worker will cover approximately 40-50 women. A team of 4*-5* trained nurses will obtain all baseline measurements (anthropometry, sociodemographic characteristics and obstetric history, diet, blood samples) at recruitment. They will also collect similar data for infants as well as blood and breast milk samples from mothers and *assist in measuring visual and auditory evoked potentials* and monitoring the birth outcomes to be collected as part of routine hospital procedures. All infant measurements will be done at the study headquarters in the IMSS General Hospital I. Mothers will be scheduled to bring their infants at 1, 3, 6, 9, 12 and 18 months, at which time growth and neurodevelopment outcomes will be measured. The total contact time per mother-infant pair is expected to range from 1-2 hours per visit of which the contact time for the infant ranges from 30 minutes at 9 months to 90 and 110 minutes at 12 and 18 months of age, respectively. The date of each assessment will be calculated based on birth date, plus or minus 7 days. A team of 3 trained psychologists will conduct all neurodevelopment and psychological measurements at the study headquarters. These include maternal intelligence at recruitment and the infant neurodevelopment outcomes, namely Neonatal Behavioural Assessment Scale (NBAS), Fagan and Bayley tests of motor and mental development (see section D. 2.2.1. for details). Approximately 4-5 infants will be scheduled daily (6 days a week) to be measured by the study nurse and psychologist. *Finally, two trained social workers will collect data on home environment during home visits at 6 and 12 months of age and at the study headquarters at 18 month of age.* Other study personnel will include an assistant who will coordinate all appointments and follow-up for data collection. Data entry operators (2) and lab assistants (1) will assist in data entry and cleaning and handling and analysis of biological samples at INSP.

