relationship between infant LCPUFA status and behavioral outcomes in humans[[196]](#endnote-196). The BSID consist of 3 scales: the Mental Scale (MDI), the Psychomotor Scale (PDI), and the Behavior Rating Scale *(see Appendix III for English and Spanish versions used in previous studies*). The MDI evaluates memory, habituation, problem solving, early number concepts, generalization, classification, vocalizations, and language. The PDI evaluates control of the gross muscle groups including movements associated with rolling, crawling and creeping, sitting, standing, walking, running and jumping. The PDI also tests fine motor manipulations involved in prehension, adaptive use of writing implements, and imitation of hand movements. The Behavioral Rating Scale assesses the child's behavior during the testing situation, which facilitates interpretation of the Mental and Motor Scales. The three scales are considered complementary, and each makes a unique contribution to the evaluation of the child. Each evaluation begins by administrating the recommended starting item from the age-appropriate item set. The infant’s raw summary scores on the Mental and Motor Scales are computed by adding the total number of items for which the child receives credit on each scale and all items below the basal item. The raw scores are then translated into Mental and Psychomotor Development Indices that are standardized to a mean of 100 ± 15. The average reliability is expected to range between 0.84 – 0.92 for the different components in children aged 6-18 mos. Interscorer agreement is 0.96 and 0.75 for the mental and motor scales, respectivelyError: Reference source not found. The BSID also provides guidelines for classification of these standardized scores into the categories of “Accelerated Performance” (115+), “Within Normal Limits” (85-114), “Mildly Delayed Performance” (70-84), and “Significantly Delayed Performance” (69 and below). Previous work has shown that the total duration of these tests increases with age and ranges between 25- 40 minutes per contact.

***c. Visual and Brainstem Auditory Evoked potentials, visual recognition memory and visual attention****: Since BSID assesses global development, more specific neurophysiological measures are required: visual evoked potentials (VEP), brainstem auditory evoked potentials (BAEP), visual recognition memory and visual attention.*

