ii. General linear models based on least squares fit will be used when the dependent outcomes are continuous variables such as indicators of child growth and development and nutrient intakes. Independent variables can include continuous, categorical and dummy (0/1) variables. Two approaches, Ordinary Least Squares (OLS) regression and Two Stage Least Squares (2SLS) will be used, depending on the issues addressed.

iii. Logistic regression may be used if the response variable is dichotomous (e.g. stunting defined as ht/age Z score <= -2 ). Adjusted odds ratios will be calculated to estimate risk for the independent variable of interest namely supplement use while controlling for other confounding variables.

D.4.1.2. Outcomes measured on repeated occasions: Some of the data are obtained from repeated measurements on individuals over time (e.g. length measurements at birth, 1, 3, 6, 9, 12, and 18 months of age). Such longitudinal data are very useful for describing dynamic processes which would be poorly captured by a single outcome or "point prevalence" assessment. Independent variables can also be time varying (e.g. feeding practices by time period: 0-3, 3-6, 6-9, 9-12 and 12-18 months) or fixed (e.g. household SES). Examples of the variables we will be modeling longitudinally include:

- **Child outcomes:** birth size, growth, motor and mental development
- **Determinants of interest:** Supplement group
- **Controlling for confounding variables:** SES, maternal BMI, intelligence, home environment.

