***3a. Length (18 mo) = Constant + β 1 (Supplement)+ β2 (Other confounding)* *+ β3  (Supplement * other confounding)***

***3b. Mental development ( 18 mo) = Constant + β1 (Supplement)+ β 2 (Other confounding)* *+***

***β3  (Supplement * other confounding)***

Similar models can be specified to test the hypotheses stated under specific aims 1 & 4, for example that breast milk PUFA levels and infant PUFA status at 1 month of age will be higher in the intervention group compared to ‘control’ group. Mean values of breast milk and blood levels of DHA will be used as the dependent variables. Since some outcomes will also be defined as dichotomous outcomes, some of the hypotheses will also be tested using logistic regression. For example, if the dependent variable for specific hypothesis 3a is prevalence of stunting at 18 months of age that is defined using cut-offs for height/age Z score (HAZ), the model will be as follows:

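### Examiners are assigned to infants at random but the analysis does not use examiner; a prespecified examiner factor would sharpen the Bayley comparisons, mainly motor, at almost no cost

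*Protocol*

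**What the plan says.** - **Assignment of examiners.** D.2.4 states that "all interviewers within each area of measurement will be randomly assigned to subjects using computer based algorithms", with the aim of avoiding systematic bias. The section uses interviewer broadly and covers psychological assessments, so I read it as including the psychologists.
- **Number of examiners.** D.2.1: "A team of 3 trained psychologists will conduct all neurodevelopment and psychological measurements at the study headquarters". These tests include the Bayley, Fagan and NBAS.
- **Agreement between scorers.** D.2.2.1 on the Bayley: "Interscorer agreement is 0.96 and 0.75 for the mental and motor scales". The figures appear with the instrument's other psychometric properties and carry a citation. For the team's own earlier Mexican cohort, the preliminary studies report: "Interscorer agreement/inter-tester reliability was above 90" per cent.
- **Analysis.** D.4.1 compares outcomes with and without adjustment where baseline characteristics differ significantly. D.4.2 starts from t tests and goes on to adjusted comparisons if confounders need to be controlled. The covariates named in D.4.1.2 are "SES, maternal BMI, intelligence, home environment". The example model for the 18-month mental score begins "3b. Mental development ( 18 mo) = Constant + β1 (Supplement)+ β 2 (Other confounding" and adds an interaction. No examiner term appears anywhere in D.4.
- **Measurement error.** D.2.4 provides for independent supervisor re-assessment of 10% of subjects, direct supervision of another 10%, and blinded replicate ratings by all examiners in 30 non-participating mother-child pairs, after which "we will correct effect estimates for the observed measurement error".

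**The concern.** The design makes examiner independent of treatment. Under that condition, adjusting for examiner cannot bias the DHA effect and removes whatever part of the score variance comes from one psychologist scoring consistently higher or lower than another. The stated adjustment rule does not lead there. It is driven by imbalance and confounding, whereas a randomly assigned examiner matters only for precision.

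What is at stake is the width of the confidence intervals for examiner-scored outcomes in a trial whose section E.10 names child development as the primary outcome. The Bayley motor index, with the lower of the two quoted agreement figures, has the most to gain.

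**Working it through.** **Inputs.** Table 3: motor and mental index SD 15, minimum difference 3.75, effect size 0.25. D.1.4: two-sided 5% level, 338 infants per group, 90% power. D.2.2.1: agreement 0.75 (motor) and 0.96 (mental). The share *f* of total score variance due to systematic examiner differences is not in the protocol and is varied as an assumption.

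**1. The plan's own figure.** n per group = 2(1.960 + 1.282)² / 0.25² = 336.2, rounded up to 337 (stated: 338). Power at 338 = Φ(0.25 × √(338/2) − 1.96) = Φ(3.25 − 1.96) = 0.9015 (stated: 90%). Both reproduce.

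**2. With examiner in the model**, taking 15 as the total SD: residual SD = 15√(1 − f), power = Φ(3.25/√(1 − f) − 1.96), SE of the difference = residual SD × √(2/338).

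| f | Residual SD | SE (points) | Power at 338 per group | n per group for 90% |
|---|---|---|---|---|
| 0 (or no examiner term) | 15.00 | 1.154 | 0.9015 | 337 |
| 0.04 (upper bound, mental) | 14.70 | 1.131 | 0.913 | 323 |
| 0.05 (assumed) | 14.62 | 1.125 | 0.915 | 320 |
| 0.10 (assumed) | 14.23 | 1.095 | 0.929 | 303 |
| 0.25 (upper bound, motor) | 12.99 | 0.999 | 0.963 | 253 |

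The SE, and so the interval width, shrinks by a factor √(1 − f): about 2.5% at f = 0.05 and 5% at f = 0.10.

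**3. Why 0.25 and 0.04 are only upper bounds.** They are 1 − 0.75 and 1 − 0.96. Disagreement between scorers also includes random scoring error, which an examiner factor cannot remove.

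**4. If SD 15 excluded examiner variance.** The total SD would be 15/√(1 − f), and unadjusted power would be 0.886, 0.869 and 0.804 at f = 0.05, 0.10 and 0.25. The examiner term would bring it back to about 0.90. D.2.2.1 describes the indices as standardised to an SD of 15, which favours reading 15 as a total SD.

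**5. Validity.** Simulation: three randomly assigned examiners, 338 per group, 4,000 runs per setting.

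| f | Type I error, no term | Type I error, with term | Power, no term | Power, with term |
|---|---|---|---|---|
| 0.05 | 0.053 | 0.053 | 0.907 | 0.922 |
| 0.10 | 0.050 | 0.044 | 0.903 | 0.931 |
| 0.25 | 0.053 | 0.051 | 0.904 | 0.957 |

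The Monte Carlo standard error at 0.05 is √(0.05 × 0.95/4000) = 0.003, so type I error is nominal with or without the term.

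**The case against.** **The models are examples and the confounding term is open, so a separate SAP could include examiner.** This stands as a limit: the point concerns only what this protocol sets out. The protocol's rule for choosing covariates, however, gives no reason to add a factor that is neither a confounder nor a baseline characteristic.

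**Nothing fails without the term.** This stands. The sample size reproduces, type I error is nominal, and random assignment does the job D.2.4 gives it.

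**The size of the gain is assumed and its anchor is weak.** This largely stands. The 0.75 covers the motor scale only, is quoted for the instrument, and is not identified as a particular agreement statistic. If it is a correlation, it says little about constant differences between examiners. The team's own cohort reports above 90%. The SDs in Table 2 at 12 months are 9.33 (motor) and 9.01 (mental). At 9.33, a 3.75-point difference is 0.40 SD, and 338 per group gives over 99% power without the term. If 18-month SDs are similar, almost no power is left to gain at that difference, though the interval would still narrow in the same proportion.

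**Examiner error is already addressed.** In part. Training, re-assessment and the 30-pair study are real safeguards, and the replicate data would help show whether examiner differences matter. But additive scoring error unrelated to a randomised treatment does not bias a mean difference; it adds variance. Correcting effect estimates rescales them and leaves examiner variance in the error term.

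**Conclusion.** The point holds as a low-severity, nearly free improvement. D.4 leaves any systematic examiner difference in the residual although the design would allow its removal without bias. For an assumed examiner share of 5% to 10%, power for the Bayley motor index at 0.25 SD would go from about 90% to between 91.5% and 93%. For the mental index the quoted agreement caps the gain at about 91.3%. These figures rest on SD 15 being the total SD and on the assumed share.

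A reader might infer more, and the documents do not support it:

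- **That the DHA comparison is biased or its tests invalid.** Examiners are assigned at random and the study team is blinded to treatment.
- **That the trial falls short of its stated power.** That follows only if SD 15 excludes examiner variance, which the protocol does not say.
- **That a quarter of motor score variance comes from examiners.** That figure is an upper bound, not an estimate.
- **That the Fagan, NBAS or nurse-measured anthropometry lose a comparable amount.** The protocol gives no agreement figure from which to size a gain there.

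**What to change.** Record the identity of the psychologist on the form at each Bayley session. Add a sentence to D.4 stating that analyses of the Bayley motor and mental scores include examiner as a prespecified fixed factor, whether or not the groups differ on it, with a further level for any replacement psychologist. The same term may be used for the Fagan and NBAS, without a claimed gain. Next to it, state that the 30-pair reliability study and its correction serve a different purpose and do not replace the examiner term.

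The cost is one form field, one or two sentences, and two degrees of freedom out of 674 (676 infants less two group means). If examiners turn out not to differ, almost nothing is lost. The change should be made before unblinding.

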**D.3. Data entry and management *(revised)***

All data forms will be checked for accuracy and completeness by the study supervisors and by the data entry operators at INSP. All data forms will be sent weekly to the data entry center at INSP and 100% double-entered into the project’s computer files using FoxProTM *.* Incorrect entries and missing data will be checked and verified on a systematic basis using range checks for values beyond permissible values and missing values. *All datafiles will be routinely backed up using read-writable CDs and copies will be kept at INSP and Emory University.*

**D.4. Data Analysis**  *(no changes*)

**D.4.1. Overview of Statistical Approach**:

Generally, we will analyze outcomes from birth to 12 months of age among all children who reach that time point. In further analyses to be conducted in the subsample of children who are followed up until 18 months of age, missing interim endpoints will be imputed using multiple imputation procedures as described by Little and Rubin[[228]](#endnote-228). Effectiveness of randomization will be examined by comparing the two groups on key baseline characteristics. In the case of significant differences, group differences in outcomes will be examined with and without adjusting for these factors. Loss to follow-up is expected to be 20% to 18 months. We will assess selection bias by comparing baseline characteristics of subjects with and without the outcome measure of interest and control for any observed differences in the analyses.

All statistical analysis will be done using Statistical Analysis Software (SAS)[[229]](#endnote-229). A probability of p<0.05 will be considered statistically significant for all hypothesis testing. Assumptions of normality will be assessed using plots and tests of normality. Non-normal variables will be transformed or categorized as required. Descriptive data analysis will include examining the distributions of neurodevelopment, dietary intakes, anthropometric and PUFA status. Means, standard deviations, quartiles and median levels will be reported. Individual analytical hypotheses will be tested using the following general statistical techniques:

D.4.1.1. Outcomes measured at one time point: These are analyses which model outcomes collected at one point in time as a function of variables collected either cross-sectionally or longitudinally. For example, cognitive development at 18 months may be modeled as function of prenatal and postnatal growth, diet, and social confounding factors. These analyses can take several forms.

i. Analysis of Covariance will be used for comparison of means of two or more categories (e.g. supplement groups) adjusting for covariates, which may be either continuous or categorical.

ii. General linear models based on least squares fit will be used when the dependent outcomes are continuous variables such as indicators of child growth and development and nutrient intakes. Independent variables can include continuous, categorical and dummy (0/1) variables. Two approaches, Ordinary Least Squares (OLS) regression and Two Stage Least Squares (2SLS) will be used, depending on the issues addressed.

iii. Logistic regression may be used if the response variable is dichotomous (e.g. stunting defined as ht/age Z score <= -2 ). Adjusted odds ratios will be calculated to estimate risk for the independent variable of interest namely supplement use while controlling for other confounding variables.

D.4.1.2. Outcomes measured on repeated occasions: Some of the data are obtained from repeated measurements on individuals over time (e.g. length measurements at birth, 1, 3, 6, 9, 12, and 18 months of age). Such longitudinal data are very useful for describing dynamic processes which would be poorly captured by a single outcome or "point prevalence" assessment. Independent variables can also be time varying (e.g. feeding practices by time period: 0-3, 3-6, 6-9, 9-12 and 12-18 months) or fixed (e.g. household SES). Examples of the variables we will be modeling longitudinally include:

- **Child outcomes:** birth size, growth, motor and mental development
- **Determinants of interest:** Supplement group
- **Controlling for confounding variables:** SES, maternal BMI, intelligence, home environment.

The analytic complexities that are introduced by this approach can be addressed using methods that have been developed recently for handling longitudinal/repeated measures data, namely Generalized Estimating Equations (GEE) approach and mixed models. The GEE approach is useful for analyzing either discrete or continuous longitudinal data and accounts for the correlation among repeated measures in the calculation of both parameter and variance estimates[[230]](#endnote-230),[[231]](#endnote-231). Additionally, it is able to accommodate time‑dependent as well as time‑independent covariates. For analyses in which the response variable is continuous and the assumption of multivariate normality is met, an alternate approach is to do mixed model analyses, using, for example, the SAS procedure PROC MIXED[[232]](#endnote-232). This procedure allows the inclusion of both fixed and random effects and, in repeated-measures situations, is more flexible and widely-applicable than standard univariate or multivariate approaches.

D.4.1.3. Structural Equation Modeling (SEM): Structural equation modeling (also known as path analysis and simultaneous equation systems) is an advanced multivariate technique widely used for testing causal models in behavioral and social research[[233]](#endnote-233),[[234]](#endnote-234). This approach will be used to test the significance of the various pathways proposed in the conceptual framework (Figure 1) accounting for the covariance within the different constructs. SEM is also useful to test bi-directional causal relationships (eg: caregiver interaction and motor development) and longitudinal data and can incorporate latent variables. SEM is particularly suited to handle issues of endogeneity inherent in the models to be developed. In order to obtain unbiased estimates, one develops multiple equations to describe the mechanisms of the system, one for each endogenous variable. The simplest and most commonly used technique for the estimation of systems of linear simultaneous equations is the class of instrumental variables estimators [[235]](#endnote-235),[[236]](#endnote-236) of which two-stage least squares (2SLS) is the most important special case. We will use this approach extensively. Recent versions of the appropriate computer packages (eg: AMOS, EQS, PROC CALIS in SAS) for testing complex causal models by SEM will be used[[237]](#endnote-237)*.*

